## Methods

### PC4L Platform

#### Instrumental Setup

The PC4L ecosystem consists of the following:

Wearable sensors that are used by the patient for monitoring disease-related parameters in passive and interactive paradigms (eg, simple biomeasurements such as heart rate or complex biomeasurements such as motor behavior; passive measurement if initiated automatically, and interactive measurement if initiated by the patient). The wearable sensor used is the smartwatch Fitbit Versa 2 (Google LLC). Patients will wear the sensor in the dominant armThe PC4L app for processing data directly from the smartphone (Samsung A20 or another similar model) inertial measurement unit sensors and GPS and directly from users. In particular, the data collected will be anthropometric data and symptoms, as well as data related to medication uptake, which are to be provided directly by the patient or the caregiver, via short questionnaires and annotations. Data related to motor behaviors through GPS and inertial sensorsDepth camera that will be deployed in the clinical centers (rehabilitation) for monitoring motor parameters of the patients. In principle, cameras will collect both 2D and 3D images to facilitate the extraction of events (eg, falls, loss of balance, wandering episodes), point trajectories, and “skeleton” data from patients for extraction of different motor behaviors and movements (eg, freezing, festination). The selected camera is the Intel RealSense depth camera (model D435)Tablet or computer to collect data related to cognitive abilities of the patients: the cognitive games app includes 6 different games about short-term memory, visual recognition, understanding, semantic memory, vocabulary, and mathematics. This app collects not only the results of the games, but also information related to the user interaction with itA local computer collects data from the patients via the sensorial ecosystem, which includes several fixed and dynamic sensors such as wearables, sensors, and cameras

In addition, the PC4L integrated care platform (accessible via internet browsers) provides an electronic health record or personal information sheet (fed with data provided by the PC4L ecosystem) and complex interface for personalized interaction and communication between patients and health care professionals.

#### PC4L Mobile App

The PC4L app includes a prescription dashboard, which monitors drug compliance; questionnaires on health status and physical activity, to be filled periodically; a symptom diary, which registers the symptoms experienced by the patient (ie, falls, freezing, loss of balance); physical activity recommendations; and daily personalized notifications on physical activity, hydration, and nutrition.

#### Decision Support System

As part of the decision support system, the PC4L platform includes a recommendation component. This component collects information from different sources available (directly from sensors, from the cognitive games, from the patients’ and users’ questionnaires, and from the multimodal fusion engine), and under clinical and health care professional guidance, after the assessment of the potential improvement or worsening of the patients’ conditions, issues personalized recommendations to address the problems identified. Recommendations are related to the following major areas: physical activity, sleep, cognitive, nutrition, social support, and stress management (for informal caregivers).

These recommendations are sent generally to the PC4L app installed on the patients’ mobile, where they appear as pop-up notifications when received. In most cases, the content of the notifications is readily available in the app in case the patient wants to check it again at a later time.

Under clinical supervision, the decision support system will indicate scores’ impacts and the contributions to either the improvement or the worsening of the patients’ health conditions. Finally, these decisions lead the recommender engine to provide personalized recommendations such as physical activity, nutrition, social support, and stress management. Additionally, reminders for therapy adherence to improve patients’ quality of life can be integrated.

Multimodal fusion aims to predict deviations from patients’ daily/normal routines, taking into consideration the input modalities (ie, cognitive state, medication intake, motor symptoms, sleep, physical activities, comorbidities, and patient’s profile). It focuses on detecting deviations in motor functions, cognitive abilities, sleep routines, and physical activities. The fusion approach benefits from domain knowledge and uses it in a computational framework to fuse the input modalities and detect the probability of deviations in the patient’s condition to support them. The multimodal fusion brings together the input modalities to enhance decision-making and gives stronger inferences using dynamic and personalized fusion through Bayesian networks. In the fusion approach, health care professionals use the patients’ profile information and the static scores to incorporate their knowledge regarding a patient into the fusion algorithm. In other words, the multimodal fusion algorithm utilizes the long-term analysis of the behavioral analysis modalities to gather broader insights into the deviations in patients’ health conditions and routines.

#### Metrics

During the monitoring period, specific metrics (Table 1) are collected, continuously and passively, through the PC4L system.

**Table 1 table1:** Metrics and related devices used during patients’ monitoring.

Metrics	Devices
Walking parameters	Wristband and phone
Bradykinesia	Wristband and phone
Loss of balance	Cameras
Falls	Cameras and wristband
Festination	Wristband and phone and camera
Physical activity	Wristband
Freezing	Wristband and phone and camera
Inactivity	Wristband
Compliance with medication	App
Sleeping pattern	Wristband
Interaction patterns with the devices	Platform or app
Usage of the physical activity recommendation services	Number of clicks per week of the different services

#### PC4L System Versions

Two different versions of the PC4L system were used (Figure 1): a fully equipped version, with all the devices enumerated above provided to the patients, and a cloud-based system that only requires a smartphone and a wearable sensor. Of those patients using the PC4L system, 25.1% (70/279) used the fully equipped version, whereas the remaining ones (209/279, 74.9%) used the cloud-based system.

**Figure 1 figure1:**
[figure not shown]
Illustrations of the PC4L solutions. API: application programming interface; PC4L: Personalized Integrated Care Promoting Quality of Life for Older People.

### Study Design

A prospective multicenter clinical study is conducted in 5 European countries: Germany, Italy, Portugal, Romania, and Spain (also including 6 pilot centers).

The pilot sites are (1) Asociacion Parkinson Madrid (APM), Madrid (Spain); (2) Casa di Cura del Policlinico (CCP), Milano (Italy); (3) Campus Neurológico Sénior (CNS), Lisbon (Portugal); (4) University and Emergency Hospital of Bucharest (UHB), Bucharest (Romania); (5) University of Medicine and Pharmacy (UMF), Bucharest (Romania); and (6) Wohlfahrtswerk für Baden-Württemberg (WBW), Stuttgart (Germany).

There are also 3 different scenarios: (1) rehabilitation center (inpatients and outpatients); (2) day care centers; and (3) home set (ie, patients’ home).

The duration per patient, at home and in the day care center, will be up to 3 months. Participants in the rehabilitation center participated during the period of their stay in the center (not exceeding the 3 months).

A specific route diagram is presented in Figure 2 in accordance with the CONSORT (Consolidated Standards of Reporting Trials) guidelines. The protocol of this study was developed in accordance with the SPIRIT (Standard Protocol Items: Recommendations for Interventional Trials) guidelines (Figure 3) [12]. The schedule of enrollment, interventions, and assessments is presented in Figure 3.

**Figure 2 figure2:**
[figure not shown]
Flowchart of the proposed randomized controlled trial according to the CONSORT (Consolidated Standards of Reporting Trials) guidelines.

**Figure 3 figure3:**
[figure not shown]
SPIRIT (Standard Protocol Items: Recommendations for Interventional Trials) diagram describing the schedule of enrollment, interventions, and assessments. *only for the EG intervention branch. AD: Alzheimer disease; BI: Barthel Index; CDRS: Clinical Dementia Rating Scale; CIRS-G: Cumulative Illness Rating Scale-Geriatric; FES-I: Falls Efficacy Scale International; MDS-UPDRS: Movement Disorder Society -Unified Parkinson's Disease Rating Scale; mHealth: mobile health; OD: other dementia; PACIC: Patient Assessment of Chronic Illness Care electromyography; PD: Parkinson disease; PSQI: Pittsburgh Sleep Quality Index; SAPS: Short Assessment of Patient Satisfaction; STAI: State-Trait-Anxiety-Inventory; SUS: System Usability Scale.

### Selection Criteria

The inclusion and exclusion criteria of participants are shown in Textbox 1.

Participant inclusion and exclusion criteria.
**Inclusion criteria**
For patients with Parkinson disease (PD) and Parkinsonism:Patients diagnosed with PD according to the Movement Disorder Society (MDS) criteriaHoehn and Yahr stages between II and IV assessed in the “on” stateFor patients with Alzheimer disease (AD) or other dementia (OD):Clinical diagnosis of AD or ODGeneral inclusion criteriaWilling to participateAged 65 years or olderWilling to interact with technology devicesWilling and able to provide written informed consent to participate in the study or having a legal representative responsible for signing
**General exclusion criteria**
Clinically significant and severe cognitive decline or intellectual disability that may compromise their ability to use a mobile phone or other electronic devicesFever or acute infection such as COVID-19 or influenzaLife-threatening coexisting disease with life expectancy
**Additional criteria regarding the different scenarios**
Home set scenario: Living at home with or without caregiverRehabilitation center scenario: Enrolled in a rehabilitation program with or without caregiverDay care center scenario: Being in the day care center program with a caregiver

### Recruitment

Patients with PD and other parkinsonian syndromes, AD, or ODs were invited to participate from the clinical centers involved in the study. Each participant organization was assigned to recruit a number of participants related to their skills, experience, number of researchers involved, and access to users (Table 2).

**Table 2 table2:** Distribution of participants per clinical center and scenario.

Scenario/clinical center	Rehabilitation (n=204), n	Day care (n=82), n	Home (n=272), n	Total (N=558), n
APM^a^	80	N/A^b^	26	106
CCP^c^	63	N/A	62	125
CNS^d^	46	N/A	86	132
UHB^e^	15	N/A	15	30
UMF^f^	N/A	30	30	60
WBW^g^	N/A	52	53	105

^a^APM: Asociacion Parkinson Madrid.

^b^N/A: not applicable.

^c^CCP: Casa di Cura del Policlinico.

^d^CNS: Campus Neurológico Sénior.

^e^UHB: University and Emergency Hospital of Bucharest.

^f^UMF: University of Medicine and Pharmacy.

^g^WBW: Wohlfahrtswerk für Baden-Württemberg.

To reach the planned number of recruits, many strategies were implemented: participants were contacted through online webinars; through brochures placed in specific centers such as pharmacies, leisure centers, and medical offices; and through patients’ associations. Further, regular updates were posted via online newsletters on different websites, such as the PC4L website and end users organizations’ websites. In addition, information about the PC4L pilot 3 study was shared during national and international conferences. Recruitment was also promoted in a collaborative way thanks to partners from other European projects. Finally, participants were recruited in person when accessing the medical facilities and via phone contact or emails after searching local databases.

Patients who discontinue the study participation because of medical conditions (ie, infections, falls, medical emergencies) or unwilling to participate any longer for other reasons (ie, difficulty with technology, loss of interest) will be considered dropouts.

### Randomization

Patients were randomized in a ratio of 1:1 to the intervention group (use the PC4L system) or the control group (no intervention) by an independent, nonclinical partner of the project consortium.

Patients allocated in the intervention group were randomized in a ratio of 3:1 to the “cloud-based solution” and the “fully equipped” PC4L system version.

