#### Intervention Group

The patients recruited and assigned to the experimental group received specific instruction in using the project platform, but without any specific program concerning the activities.

Specifically, patients, after the baseline assessment, received the instrumental setup and indications on its functionalities. Patients were instructed about the use of the Fitbit, the PC4L app, and the cognitive games on a tablet or computer. Patients were also provided with manuals.

Specifically, according to the study approach detailed by Biehl et al [9], the patients were instructed to complete the following questionnaires in the app during the first week and during the last week of the study period: the 10-item Eating Assessment Tool (EAT10) [13] for evaluation of dysphagia; the Edmonton Symptom Assessment System (ESAS) [14] and the Patient Global Impression (PGI)—Severity [15] for evaluation of symptoms; and the International Physical Activity Questionnaire (IPAQ) [16] for evaluation of physical activity. In addition, during the last week of using the app, patients were requested to complete the SUS [17], via the app, for evaluation of usability.

The platform was installed in each scenario with the assistance of the project research staff (ie, bioengineers).

A total of 2 versions of PC4L systems were installed: while the cloud-based system (which only required a smartphone and a wearable sensor) was used in all scenarios, a fully equipped version was implemented only in the rehabilitation scenario.

The patients received the same directions in all 3 scenarios.

At the end of the study period, patients performed end-of-study evaluations and returned the instrumental setup.

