#### Usability and Satisfaction Assessment

At the end of the experimental period, patients allocated to the experimental group performed the usability evaluation of the PC4L platform solution by means of the SUS [17], Global Satisfaction and mHealth User Satisfaction questionnaires, adverse events reporting, and end-of-study open questions.

The SUS is used to measure how easy or difficult the proposed system is to use. We will compare the usability of 2 different versions of the PC4L system (fully equipped and cloud-based solutions). The overall SUS score will be calculated and assessed consistently with the literature: a score of 100 corresponds to the best imaginable usability, while acceptable usability is defined by an SUS score above 68 points [17,25].

The Global Satisfaction Questionnaire is used to assess the overall level of satisfaction or dissatisfaction with the platform experience.

The mHealth User Satisfaction questionnaire is used to measure user satisfaction and usability of the recommendation component of the solution [26].

As a completion of end-of-study assessment, an adverse events report and end-of-study open questions of preferred and less preferred aspects of the platform, as well as suggestions for improvements, will be collected for each user.

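### The stated 3:1 version randomisation, the 70/209 split and the rehabilitation-only use of the fully equipped version cannot all be true, and an unrestricted usability comparison of the versions would be confounded with setting

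*Protocol article*

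**What the plan says.** - Protocol article, Randomization: after the 1:1 allocation to intervention or control, "Patients allocated in the intervention group were randomized in a ratio of 3:1 to the" cloud-based and fully equipped versions. No scenario is excluded.
- PC4L System Versions: "25.1% (70/279) used the fully equipped version, whereas the remaining ones (209/279, 74.9%) used the cloud-based system".
- Intervention Group: the cloud-based system "was used in all scenarios", whereas "a fully equipped version was implemented only in the rehabilitation scenario". Instrumental Setup agrees, since it places the depth cameras in the rehabilitation centres.
- Recruitment, Table 2: the column "Rehabilitation (n=204), n" stands beside 82 day-care and 272 home patients, 558 in total over both arms.
- Usability and Satisfaction Assessment: "We will compare the usability of 2 different versions of the PC4L system (fully equipped and cloud-based solutions". The Aims list the same comparison of versions as an objective. Neither place limits it to one scenario.
- Study Design: rehabilitation patients take part for the length of their stay, at most 3 months; home and day-care patients take part for up to 3 months.

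**The concern.** A patient can be randomised between two versions only where both are available. By the article's own account that is rehabilitation, which holds a little over a third of the patients. Yet the user counts match a 3:1 split of the whole intervention group. At least one of the statements on allocation, availability or numbers must therefore be wrong or incomplete.

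What is at stake is the comparison of the two versions. If every fully equipped user is in rehabilitation and most cloud users are not, a difference in SUS may reflect where patients were, how long they used the system and which centre looked after them, as well as the version. The Randomization section, as worded, invites a reader to take 70 versus 209 as a randomised contrast.

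**Working it through.** **Inputs.** Intervention group 279, with 70 fully equipped and 209 cloud (PC4L System Versions). Patients by scenario over both arms: 204, 82 and 272 (Table 2; rows and columns add up to 558). Ratios 1:1 and 3:1 (Randomization). The SUS standard deviation of 18 and the setting differences of 5 and 10 points are my assumptions; the article gives no figure for either.

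**1. The plan's own figure.** 279/4 = 69.75, so 70 and 209 (25.1% and 74.9%). The split is 3:1 over the whole intervention group.

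**2. Expected intervention patients by scenario at 1:1.** Rehabilitation 204/2 = 102; day care 82/2 = 41; home 272/2 = 136. Home and day care together: 177. If the 1:1 allocation was not stratified by scenario, the rehabilitation count is hypergeometric with mean 102 and SD √[279 × (204/558) × (354/558) × (279/557)] = 5.69, so the 95% range is about 91 to 113.

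**3. Reading A: 3:1 over all 279.** Expected full systems outside rehabilitation: 70 × 177/279 ≈ 44. This contradicts the Intervention Group section. The probability that all 70 fall among the 102 rehabilitation patients by chance is C(102,70)/C(279,70) ≈ 3 × 10⁻⁴¹.

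**4. Reading B: 3:1 within rehabilitation only.** Expected full systems: 102/4 = 25.5, about 26. Even if all 204 rehabilitation patients were in the intervention group, 204/4 = 51. Seventy would need 70 × 4 = 280 rehabilitation intervention patients. So this reading fails whatever the split between arms.

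**5. If all 70 were in rehabilitation.**

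| Rehabilitation intervention patients | Full share there | Cloud users there | Cloud users elsewhere |
|---|---|---|---|
| 91 | 77% | 21 | 188/209 = 90% |
| 102 | 69% | 32 | 177/209 = 85% |
| 113 | 62% | 43 | 166/209 = 79% |

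Within rehabilitation the split would be about 70 to 32, or 2.2:1 towards the full version, the opposite direction from the stated ratio.

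**6. How much of a setting difference enters the contrast.** Let rehabilitation and other patients differ by D SUS points, with no version effect. The full group carries all of D and the cloud group carries 32/209 of it, so the contrast is D × (1 − 32/209) = 0.85 D (0.79 D to 0.90 D over the range in step 2). For illustration only: D = 5 gives about 4.2 points and D = 10 about 8.5.

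**7. Precision at an assumed SD of 18.** Half-width of the 95% interval = 1.96 × SD × √(1/n₁ + 1/n₂).
- 70 versus 209, ignoring setting and centre: 1.96 × 18 × 0.138 = 4.9 points.
- 70 versus 32, within rehabilitation: 1.96 × 18 × 0.213 = 7.5 points.

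**8. Other differences that travel with version.** Exposure time follows from Study Design. As to centre, two of the six (UMF with 60 patients, WBW with 105) have no rehabilitation patients. At 1:1 they supply about 165/2 ≈ 82 cloud users and no fully equipped ones.

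**The case against.** The strongest reply is that this is a condensed article. The analysis set for the version comparison, and any restriction or adjustment by scenario, may be laid down in a full protocol or analysis plan that is not shown. The usability section does not call the comparison randomised, nor does it fix 70 versus 209 as its population. This stands, so silence about the analysis set is not the finding. The finding is that printed statements about allocation, availability and numbers collide, together with what follows if the comparison is run unrestricted.

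A reader might infer that version was really randomised within rehabilitation, at about 2:1 towards the full version. The documents do not show this. Version may have been allocated by availability of equipment, or one of the sections or counts may be misreported.

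A reader might also infer that a spurious version effect will be declared significant. The documents do not support that either. The Statistical Analysis section names paired and correlation tests only, and SUS is collected once, at the end, so no stated test applies to the version contrast; it may be descriptive. The outcome also depends on the assumed setting difference: at an SD of 18, 10 points would give a contrast above the half-width and 5 points would not.

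Three further points carry partial weight. The figure of 102 assumes 1:1 within scenario, and Table 2 may show planned numbers; yet even 204 falls short of the 280 needed. Patients had the same directions in every scenario, and research staff helped with each installation, which may narrow setting differences but does not remove them. All four rehabilitation centres also enrolled home patients, so centre is only partly confounded.

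**Conclusion.** The contradiction stands and does not depend on how the arms divided within rehabilitation. The size of the confounding does: it assumes that all 70 full systems were in rehabilitation and that about 102 (91 to 113) intervention patients were there. On that footing an unrestricted version comparison is not randomised, and most of any setting difference passes into it. The SUS points are illustrations, because neither the setting difference nor the SD comes from the article. It would go too far to say that the version result must be due entirely to setting; the documents show that the two cannot be separated in an unrestricted contrast, not which one drives it.

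The matter is an internal contradiction bearing on a secondary usability objective. It should be fixed, but it leaves the comparison of intervention with control on EQ-5D-3L untouched.

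**What to change.** 1. Reconcile the PC4L System Versions, Randomization and Intervention Group sections: state which patients were eligible for each version, how version was allocated, and the ratio used among them. Correct the 70/209 counts if they are what is wrong.
2. Define the SUS comparison of versions, and any other version comparison, among rehabilitation intervention patients only, adjusted for centre. Describe it as randomised only if version was in fact randomised there.
3. Report home and day-care cloud users descriptively. If a contrast of all 70 with all 209 is shown, label it non-randomised and confounded with setting.

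The cost is wording and a smaller analysis set; enrolment is closed and no new data are needed. The downside is lost precision, with the half-width rising from about 4.9 to about 7.5 SUS points at the assumed SD of 18 with about 70 versus 32 patients. The narrower figure belongs to a contrast that does not isolate the version.
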